### Study setting

The transition services program will be evaluated in patients under the care of a hospitalist at a tertiary hospital and a smaller satellite hospital, both located within a large integrated healthcare system in Charlotte, NC, USA.

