### Risk score

The readmission risk model used is a neural network. It is built from a final set of 71 variables after the assessment of several thousand variables consisting of demographic, clinical, and use data. The model was built using retrospective information but is applied in a nearly real-time setting during a patient’s inpatient admission. Model performance was determined using a training dataset (70%) as well as a testing dataset (30%), as is typical in predictive model development. Operationally, scoring data for the model are sourced from a patient’s billing history (at the time of admission) as well as using clinical data updated throughout the hospital stay. Examples of information leveraged in the model include variables such as albumin, ammonia, body mass index, fall risk score, inability to verbalize needs, insurance type, living situation, oxygen flow rate, and pain intensity.

Every 1–4 h, a patient’s readmission risk is assessed via the model, and a risk score between 0 and 1 is calculated. This value is then attributed to one of four segments that convey increasing risk of readmission (low, moderate, high, or very high). Outside this study, clinicians use this risk information to assist in discharge planning.

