### Sample size

This study is designed to detect a 30% relative reduction in the readmission rate, with the usual care group assumed to have a 20% readmission rate in 30 days. A relative reduction of 30% was based on estimates from randomized controlled trials looking at bundled transition interventions and intensive home interventions [9, 20–22]. We will have 80% power to detect this reduction (transition services group rate reduced to 14%) with a total sample size of 1230 (α = 0.05) using a chi-square test for independence. Assuming 10% of those assigned to transition services will not participate, we must increase our sample size to 1520 (*n* = 760 per arm) to account for the anticipated decrease in the effect size. At the time of protocol design, available historical data included only the more narrow CMS definition of single-site readmissions (secondary outcome). Thus, the assumptions used in the power analysis are reflective of more conservative estimates than would be expected for the primary outcome measure’s expanded definition for readmission, which includes inpatient and observation stays between any of the acute care hospitals.

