### Analysis

All analyses will follow intention-to-treat principle such that patients will be analyzed on the basis of the group to which they were initially randomized, but after reapplication of inclusion and exclusion criteria at the time of hospital discharge (Fig. 1, “Eligible at discharge” bubble). Baseline comparisons of the two groups will be made using univariate analyses such as the *t* test and chi-square test. The primary outcome, readmission in 30 days, will be compared between the two groups of patients who are eligible at discharge, using logistic regression. Results will be presented with ORs and 95% CIs. In addition to the intention-to-treat analysis, we will perform a per-protocol analysis to evaluate the patients who are eligible at discharge and participate in the transition services program compared with usual care patients who are eligible at discharge. For all outcomes, we assume that if there are no visits in the electronic medical record, the value for having a visit is null; therefore, there will be no missing data for the primary or secondary outcome measures.

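### The odds ratio is the only effect measure named for the primary comparison, although the trial is sized and monitored on a 30% reduction in the readmission rate; no covariate is named

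*Protocol article*

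**What the plan says.** The Analysis section of the protocol article states that the primary outcome is compared between the two groups "using logistic regression. Results will be presented with ORs and 95% CIs". No other effect measure and no covariate is named there.

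Elsewhere the article works in risks. The Sample size section says the study is "designed to detect a 30% relative reduction in the readmission rate". It takes 20% as the control rate and sizes the trial with a chi-square test on 20% against 14%. The section on the interim analysis computes conditional power under the same 30% reduction. The Fig. 3 caption words the primary outcome as a difference in rates.

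Two baseline variables are relevant. The Risk score section says that "a risk score between 0 and 1 is calculated" every few hours, and eligibility depends on that score. Patients are treated "at a tertiary hospital and a smaller satellite hospital". The Randomization and blinding section describes blocks of six and mentions no stratification factor.

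**The concern.** The effect measure fixed for reporting is not the quantity the trial was designed to detect. Readmission is common here, so the odds ratio lies further from 1 than the risk ratio. A reader who takes an odds ratio as a relative reduction in readmissions will overstate the benefit. An odds ratio of 0.70 would look like the design target when it falls short of it. The intended readers are health systems deciding on investment, and the absolute difference is the figure they can most readily use.

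The odds ratio is also non-collapsible: adding a prognostic covariate changes the quantity estimated even when the effect on risk does not change. With no covariate named, the article does not say whether its odds ratio is marginal or conditional. Finally, a score built to predict readmission is an obvious covariate, so some precision may be available at little cost.

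**Working it through.** **Inputs.** From Sample size: control rate 20%, intervention rate 14%, 80% power, α = 0.05, total 1230, 10% non-participation, final total 1520 (760 per arm). From Randomization and blinding: 1:1 allocation. The score's discrimination is not given, so an AUC of 0.55 to 0.75 within the enrolled patients is assumed.

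**1. The plan's own figures.** The pooled-variance chi-square formula, two-sided, is

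n per arm = [1.960·√(2·p̄·(1−p̄)) + 0.842·√(p₀(1−p₀) + p₁(1−p₁))]² / (p₀−p₁)².

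With p₀ = 0.20, p₁ = 0.14 and p̄ = 0.17 this gives 615 per arm, total 1230, as stated. With 10% non-participation the intervention rate becomes 0.9 × 0.14 + 0.1 × 0.20 = 0.146, which gives a total of 1540. The shortcut 1230/0.9² = 1518.5 rounds to the stated 1520. Power at 760 per arm for 20% against 14.6% is 79.5% by the chi-square formula and 79.2% for the Wald test of an unadjusted logistic model, so sizing and test agree.

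**2. The design effect on three scales.** OR = [p₁/(1−p₁)] / [p₀/(1−p₀)].

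| Control | Intervention | Risk ratio | Risk difference | Odds ratio |
|---|---|---|---|---|
| 20% | 14% | 0.70 | −6.0 points | (0.14/0.86)/(0.20/0.80) = 0.651 |
| 20% | 14.6% | 0.73 | −5.4 points | 0.684 |
| 15% | 10.5% | 0.70 | −4.5 points | 0.665 |
| 25% | 17.5% | 0.70 | −7.5 points | 0.636 |
| 30% | 21% | 0.70 | −9.0 points | 0.620 |

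**3. The reverse reading.** If the observed odds ratio is 0.70 at a 20% control rate, the intervention odds are 0.70 × 0.25 = 0.175. The risk is 0.175/1.175 = 14.9%, and the relative reduction is 1 − 0.1489/0.20 = 25.5%. At a 30% control rate the same odds ratio means 23.1% against 30%, a reduction of 23.1%.

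**4. One result, three presentations.** If exactly 20% and 14.6% were observed with 760 per arm:
- odds ratio 0.684 (95% CI 0.523 to 0.895)
- risk ratio 0.730 (0.584 to 0.912)
- risk difference −5.4 points (−9.2 to −1.6)

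**5. What adjustment would add.** Simulation of 3000 trials per row, 760 per arm, 20% against 14.6%, one normally distributed baseline covariate. Simulation error of each power is about 0.7 points.

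| Assumed AUC | Power unadjusted | Power adjusted | Conditional odds ratio |
|---|---|---|---|
| 0.55 | 80.3% | 80.5% | 0.683 |
| 0.60 | 78.9% | 80.3% | 0.679 |
| 0.65 | 80.3% | 81.1% | 0.672 |
| 0.70 | 79.1% | 83.2% | 0.662 |
| 0.75 | 80.1% | 85.2% | 0.646 |

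In every row the marginal risks are the same (20% and 14.6%), yet the conditional odds ratio drifts from the marginal 0.684 down to 0.646. A standardized risk difference or risk ratio keeps one target whichever model is used.

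**The case against.** The strongest reply is that this is a condensed article and the SAP is not shown. A reader might infer that the model contains treatment group alone, that nothing but an odds ratio will be reported, and that the score and hospital go unused. The text says none of these. It is silent on covariates, which an article commonly leaves to the SAP. The Outcomes section also says that substantial program changes will be incorporated into the outcome analyses, so the model content is not closed.

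A reader might also infer that an unadjusted analysis would be wrong. It would not: randomization makes it valid, and no stratification factor is described that would call for adjustment. Nor can adjustment be offered as a remedy for re-applying the eligibility criteria at discharge, because a baseline score and hospital would not reliably remove selection that depends on later events.

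It is also fair to say that arm rates are normally reported with a binary outcome, that an unadjusted odds ratio can be converted once they are, and that costs have their own planned analysis.

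All of this stands, and it limits the point. It does not remove the mismatch between the one effect measure the article names and the rate reduction on which it sizes and monitors the trial. Conversion from arm rates also fails for an adjusted odds ratio.

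**Conclusion.** The point holds for the effect measure: the reporting scale named for the primary comparison is not the scale of the design target. At the design rates the target risk ratio of 0.70 appears as an odds ratio of 0.651, which a careless reader would take as a 35% reduction. Over control rates of 15% to 30% it appears as 0.665 to 0.620. The larger gap applies if the control rate exceeds 20%. The Sample size section points that way by calling its assumptions conservative for the broader primary definition, but it gives no figure. This is a matter of interpretation and reporting; type I error, sample size and the validity of the test are untouched.

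The covariate part is a supporting recommendation, not an error in the plan. Its gain rests on an assumed AUC: roughly 0 to 1.5 points of power at 0.55 to 0.65, and 4 to 5 points at 0.70 to 0.75. Enrolment is restricted to high-risk patients, which narrows the score's range and probably puts the gain at the low end.

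**What to change.** In the Analysis section, or in the SAP if it does not already do so:

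- Name the marginal (standardized) risk difference and risk ratio, each with a 95% CI, as the headline result for 30-day readmission. Keep the odds ratio as secondary and show both arm rates.
- Prespecify the logistic model as treatment group, risk score at referral (continuous, for example on the logit scale) and hospital. Define which score counts as the one at referral, since it is recalculated every 1 to 4 hours. Obtain the marginal measures by standardizing over this model, and give the unadjusted comparison alongside.
- Fix the covariates in advance, not from the planned baseline t tests and chi-square tests.

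The cost is a change of wording and a little programming; sample size and conduct do not change. The score must exist before randomization because eligibility depends on it, but the Data collection section does not list score or hospital as stored fields. Confirm that both are kept for every randomized patient in both arms.

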### Trial intervention and control

Control patients will receive usual care. Standard discharge care at both hospitals includes recommendations for follow-up appointments with a patient’s primary care physician, discharge summaries sent to primary care physicians, the arrangement of home health services based on each patient’s needs, and other outreach interventions such as follow-up care management phone calls.

In addition to usual care, patients referred to the intervention group are contacted during their hospital stay by a registered nurse patient navigator, invited to participate in the transition services program, and then followed for the remainder of their hospital stay. For 30 days following discharge, patients have access to the transition services program, which, in addition to a free-standing clinic, includes the following: (a) as-needed access to transition-dedicated internal medicine, pharmacist, paramedicine, behavioral health, and care management providers; (b) hospital follow-up evaluation with a medical provider, either virtually in the patient’s home facilitated by a paramedicine provider or in the transition clinic; (c) medication reconciliation by a pharmacist; (d) at least weekly contact with the care management team; (e) 24/7 phone support, 24/7 paramedicine visit availability, and same-day clinic scheduling; and (f) coordinated transition to the next appropriate care location after 30 days (Table 1). The intensity of the care provided is not prescribed but rather dictated by the care team and patient. At a minimum to qualify as having participated, patients will have an in-person or virtual visit with the transition services medical provider. Patients or their insurance providers are charged only for services that are billable under usual care, whereas all other services are provided by the healthcare system as part of care management.

**Table 1 Tab1:** Transition services program intervention components

Transition services components	Transition recommendations [10] and drivers of readmissions addressed
Referral to transition services program and introduction by patient navigator while patient is still hospitalized	• Dedicated transition personnel • Spanning inpatient and outpatient • Engagement • Discharge plan confusion

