**Fig. 3 Fig3:**
[figure not shown]
Patient-centered readmission. *The primary outcome is the difference in 30-day readmission rates between facilities. A readmission visit can be either an inpatient or an observation visit. Secondary outcomes include the difference in 30-day readmission rates between facilities. In one analysis, a readmission visit can only be an inpatient visit, and in another analysis a readmission visit can only be an observation visit

**Table 2 Tab2:** RE-AIM (Reach, Effectiveness, Adoption, Implementation, Maintenance) framework

RE-AIM measure	Metrics
Reach: How do I reach the target population?	• Capture rate: proportion of patients interested in program participation out of those who are referred and appropriate at the time of discharge • Show rate: proportion of patients who have a visit with the program out of those who are referred and appropriate at the time of discharge
Effectiveness: How do I know my intervention is effective?	• Absolute and observed/expected 30-day readmission rates as defined by CMS and reported as a routine quality metric by the healthcare system
Adoption: How do I develop organization support to deliver my intervention?	• Qualitative evaluation of program and participating primary care providers, which will be reported separately
Implementation: How do I ensure the intervention is delivered properly?	• Absolute and mean visit counts and visit type by month for the clinic as a whole and per patient • Proportion of patients with a medicine reconciliation and provider visit in 72 h out of all participating patients
Maintenance: How do I incorporate the intervention so it is delivered over the long term?	• Institutional level: Reach, Effectiveness, and Implementation measures for 3 months after conclusion of trial • Patient level: 90-day readmission and composite ED and hospitalization rates • Patient level: Qualitative substudy evaluating effect of intervention more than 60 days after last contact

*CMS* Centers for Medicare and Medicaid Services, *ED* Emergency department

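### The supplementary per-protocol analysis admits intervention patients by a visit inside the 30-day outcome window but sets no such condition for usual care, so it leans toward benefit even with no true effect.

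*Protocol article*

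**What the plan says.** The Analysis section makes intention-to-treat among patients eligible at discharge the main comparison. It adds a per-protocol analysis of intervention patients who are eligible at discharge and "participate in the transition services program compared with usual care patients who are eligible at discharge".

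The section Trial intervention and control defines participation: "At a minimum to qualify as having participated, patients will have an in-person or virtual visit with the transition services medical provider". It lists the follow-up evaluation among services available for 30 days after discharge, held by virtual visit at home or in the transition clinic. Table 1 also describes the evaluation as taking place after discharge. The primary outcome is readmission in the same 30 days.

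The only timing figure for the visit is a process measure in Table 2 (Implementation row): "Proportion of patients with a medicine reconciliation and provider visit in 72 h out of all participating patients". It is a monitored proportion, not a condition of participation.

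Patients are invited to take part, and refusals are tracked (Data collection). For the per-protocol comparison the article states no landmark, time-dependent exposure, adjustment or matching condition for usual care.

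**The concern.** Entry to one side of the comparison depends on something that happens after the outcome clock has started; entry to the other side does not. Participants are guaranteed to be free of readmission up to their visit, while usual-care patients are counted from discharge. This is immortal-time bias. Choosing to attend is a second source of imbalance, and it would usually push the same way.

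The Discussion expects that randomising referrals may dilute the effect and leave the trial underpowered, and it intends the results to guide investment. If the primary result is null, readers will turn to the result among those who took part. An estimate that favours the programme by construction could then be read as showing that it works in patients who engage.

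**Working it through.** **Inputs from the article.** Usual-care risk: "with the usual care group assumed to have a 20% readmission rate in 30 days". Design effect: "This study is designed to detect a 30% relative reduction in the readmission rate", that is 20% against 14%. Power and size: "We will have 80% power to detect this reduction" "with a total sample size of 1230 (α = 0.05) using a chi-square test for independence". Non-participation is 10%, with a final 760 per arm.

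**Input not in the article.** q, the share of 30-day readmissions that occur before the first provider visit. It is treated as an assumption over a range.

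**Step 1. Reproduce the plan's figures.** Two proportions, two-sided 0.05, pooled variance, no continuity correction:

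n = [1.960·√(2·0.17·0.83) + 0.842·√(0.2·0.8 + 0.14·0.86)]² / 0.06² = 615 per arm, 1230 in total. This matches.

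With 10% non-participation the intervention rate is 0.9·14% + 0.1·20% = 14.6%. That needs 770 per arm (1540); 1230/0.81 = 1518.5 gives the stated 1520. Power at 760 per arm is 79.5%. The sample size is not in dispute.

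**Step 2. Participants' rate when the programme has no effect.** Let p = 0.20 in both arms. Assume that patients readmitted first never count as participants and that other non-participation is unrelated to risk. Then:

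participants' rate = p(1 − q)/(1 − pq), and usual care stays at 20%.

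The last column is the chance of p < 0.05 favouring the programme, with 760 controls and 684 participants (0.9·760). For an unbiased comparison it would be 2.5%.

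| q | Participants' rate | Risk ratio | Chance of a significant false benefit |
|---|---|---|---|
| 5% | 19.2% | 0.96 | 6% |
| 10% | 18.4% | 0.92 | 12% |
| 20% | 16.7% | 0.83 | 37% |
| 25% | 15.8% | 0.79 | 55% |
| 30% | 14.9% | 0.74 | 72% |
| 34.9% | 14.0% | 0.70 | 86% |

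**Step 3. Every visit on day 3, the one time mark in the article.**
- Readmissions uniform over 30 days: q = 3/30 = 10%, rate 18.4%, false reduction 8%.
- Readmissions declining at 0.10 per day: q = (1 − e^−0.3)/(1 − e^−3) = 27.3%, rate 15.4%, false reduction 23%.
- A constant hazard lies near the mild end: 1 − 0.8^(27/30) = 18.2%.

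With visit times spread exponentially around a mean of 3 days, simulated risk ratios run from 0.92 (uniform) to 0.80 (decline of 0.10 per day), much the same range.

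**Step 4. What it takes to reach the design effect.** Setting the participants' rate to 14% gives q = 0.06/(0.20 − 0.14·0.20) = 34.9%, so 0.20·0.349 = 7.0% of the arm is readmitted before a visit. A fixed visit day that yields this is day 10.5 with uniform readmissions, and day 7.7, 6.3 or 4.0 with decline rates of 0.03, 0.05 or 0.10 per day. If total non-participation is exactly 10%, the readmission rate among non-participants must be (0.20 − 0.9·0.14)/0.10 = 74%.

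**Step 5. The alternatives under no effect.** The complier-average effect is the risk difference between randomised arms divided by the difference in participation. With equal risks its numerator is zero whatever q is. At plan values it is (20 − 14.6)/0.9 = 6.0 points, which recovers the designed 20% against 14%. If both arms must be readmission-free at the same landmark day and are counted from there, the risk ratio is 1.00 apart from self-selection.

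**The case against.** Much of the case against concerns size, and most of it stands.

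- A reader might infer that the bias is as large as the design effect. The article does not support that. It needs about 35% of readmissions to precede the visit, and nothing is said about either timing. Same-day scheduling and round-the-clock paramedicine availability point to early contact. A 74% readmission rate among non-participants is also hard to square with a plan that separately tracks refusals and missed appointments.
- A reader might infer from the 72 h measure that late visits are expected. It shows only that visits by day 3 are not guaranteed.
- The article does not say whether a visit after a readmission counts as participation. If it does, early readmissions can re-enter the intervention side and the bias shrinks.
- A reader might take this to be the only analysis of those who engage. That cannot be known, because a statistical analysis plan may exist and is not shown.
- The analysis is supplementary. Sample size, interim rules and the primary conclusion do not rest on it.
- The complier-average effect has its own weakness. In-hospital navigator contact, follow-up calls and telephone support could act without a provider visit.

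The structure remains. The article itself names both comparison groups and defines participation, so an analysis that follows it carries the bias.

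**Conclusion.** The point holds as a should-fix. As written, the per-protocol comparison leans toward benefit through immortal time, and self-selection, not quantified here, would usually add to it. If every visit fell on day 3, the false relative reduction would be about 8% to 23%. At the mild end (q = 10%) the chance of a significant false benefit is about 12%; at the severe end (q = 27.3%) it lies between the 55% and 72% tabulated for q = 25% and 30%. Later visits make it larger.

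These figures assume 20% risk in both arms, no true effect, and no credit for visits after a readmission. A false effect equal to the 30% design target is possible arithmetically but not shown by the documents. Nor is the primary result compromised: the intention-to-treat comparison does not use participation.

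**What to change.** In the Analysis section, replace the per-protocol contrast with a complier-average causal effect among patients eligible at discharge, using randomised referral as the instrument: the risk difference between arms divided by the difference in participation, with a bootstrap or two-stage confidence interval. State the assumption that referral acts only through participation. Add a sensitivity version that counts any programme contact as participation. Because referred patients are contacted in hospital, that version will sit close to the intention-to-treat difference (5.4 points at plan values if all are contacted), so the two together show how much the assumption matters.

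If a participant-only comparison is kept, either label it descriptive and give no p-value, or apply the same readmission-free landmark day to both arms, count outcomes from that day, and say that self-selection remains. In either case state whether a visit after a readmission counts as participation for the analysis.

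The cost is a change of wording and a few lines of code; visits and refusals are already recorded. The downside is one added assumption and a wider interval than intention-to-treat, by a factor of about 1/0.9 = 1.11 on the risk-difference scale at 90% participation.
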